## Abstract

**Background:**

Emerging research suggests virtual reality (VR) techniques hold promise for mitigating cognitive decline in patients with mild cognitive impairment (MCI). Furthermore, accumulating evidence indicates that gut dysbiosis is a key factor associated with cognitive impairment. This study aims to determine whether a novel virtual reality-integrated multi-modal intervention can beneficially modulate the brain-gut axis in individuals with MCI.

**Methods:**

This study is a randomized single-blind controlled trial that will include 66 older adults with MCI from the community. Eligible participants will be randomly assigned in a 1:1 ratio to the intervention group or the waitlist group. The intervention group will complete 36 sessions (three sessions per week for 12 weeks) consisting of virtual reality cognitive training (VRCT), traditional cognitive training (TCT), and physical exercise (PE). The control group will not receive any intervention during the study period. The primary outcome is the change in a memory-weighted cognitive composite score. Exploratory outcomes: mechanistic changes along the brain-gut axis, including: (1) Changes in gut microbiota alpha/beta diversity and composition assessed by 16S rRNA gene sequencing, (2) Changes in resting-state brain activity and functional connectivity assessed by fMRI. Outcome measures will be assessed at three or four time points: baseline, mid-intervention (Week 6), post-intervention (Week 12), and at a 12-week follow-up (Week 24).

**Expected outcomes:**

We hypothesize that, relative to the waitlist control, the intervention group will demonstrate concurrent improvements in cognitive performance and a shift in gut microbiota composition toward a more favorable profile, thereby providing preliminary evidence for modulation of the brain-gut axis.

**Clinical trial registration:**

[www.chictr.org.cn], identifier [ChiCTR2400093397].

## Introduction

1

Mild cognitive impairment (MCI) is an intermediate stage between normal aging and dementia, affecting roughly 10%–15% of adults aged 65 and older (Anderson, 2019). In some cases, MCI can progress to different forms of dementia, such as Alzheimer’s disease (AD) or vascular dementia (VD) (Meyer et al., 2002). With current dementia treatments demonstrating limited effectiveness, researchers are increasingly focusing on early intervention during the MCI stage or even earlier. While pharmacological options exist, non-pharmacological interventions are currently considered the preferred approach for managing MCI (Talar et al., 2022).

Previous research has demonstrated that traditional cognitive training (TCT), physical exercise (PE), and lifestyle modifications can slow cognitive decline in individuals with MCI (Fonte et al., 2019; Ornish et al., 2024). A recent randomized controlled trial (RCT) demonstrated that a 20-week combined intervention of aerobic exercise and cognitive training led to significant improvements in Alzheimer’s Disease Cognitive Assessment Scale (ADAS-Cog-13) scores among patients with MCI (Montero-Odasso et al., 2023). Similar cognitive benefits were observed with mind-body exercises, including Tai Chi (Li et al., 2023) and yoga training (Grzenda et al., 2024). A systematic review revealed that both aerobic exercise and resistance training enhance cognitive performance in both healthy community-dwelling older adults and patients with MCI (Law et al., 2020). Another RCT study found that a 20-week lifestyle modification program significantly improved cognitive function in patients with MCI (Ornish et al., 2024). Furthermore, recent advances in non-pharmacological interventions have established computerized cognitive training (CCT) (Li et al., 2022) and virtual reality cognitive training (VRCT) (Zhong et al., 2021) as evidence-based approaches for mitigating cognitive decline in MCI.

Virtual reality (VR) is emerging as a promising and cost-effective tool for cognitive intervention and physical exercise (García-Betances et al., 2015). Its immersive, interactive, and engaging nature makes it more appealing and motivating than traditional methods, attracting growing interest in recent years (García-Betances et al., 2015). A recent systematic review indicated that VRCT is as effective as traditional approaches, while offering greater ecological validity and adaptability in the treatment of MCI (Tortora et al., 2024). A 12-week single-blind RCT study demonstrated that a VR physical and cognitive training intervention significantly improved overall cognition, delayed recall, and instrumental activities of daily living (Liao et al., 2020). Moreover, functional near-infrared spectroscopy (fNIRS) data from the VR group revealed reduced activation in prefrontal regions following the intervention, indicating improved neural efficiency (Liao et al., 2020). In addition, VR-related biomarkers have shown effectiveness in detecting behavioral patterns associated with subtle deficits in instrumental activities of daily living (Park et al., 2024). When combined with MRI-based biomarkers, such as observable structural brain changes, VR may serve as a valuable tool for the early screening of MCI (Park et al., 2024). However, the effect of combining VRCT, TCT, and PE on cognition remains largely unexplored.

Cognitive function in middle-aged and older adults has also been shown to be associated with specific gut microbiota (Aljumaah et al., 2022). This connection suggests that probiotics, prebiotics, and commensal bacteria may help slow or improve cognitive decline (Aljumaah et al., 2022). Li et al. (2019) observed similar alterations in the gut microbiota of individuals with AD and mild MCI. For instance, the genus Escherichia was found to be elevated in both fecal and blood samples from individuals with AD and MCI (Li et al., 2019). Fan et al. (2025) identified 59 key microbial species associated with biomarkers of MCI and AD. Through functional profiling, they revealed microbial pathways involved in energy metabolism and neuroinflammation, highlighting their potential role in mediating the relationship between gut microbiota and brain health (Fan et al., 2025). However, few studies have examined whether cognitive training can modulate the brain-gut axis in MCI.

We hypothesize that a multi-modal intervention, integrating VRCT, TCT, and PE, will improve cognitive performance and beneficially modulate the brain-gut axis in individuals with MCI. To test this hypothesis, we will conduct a randomized, single-blind controlled trial among community-dwelling older adults with MCI. The primary objective of this study is to investigate whether the multi-modal intervention enhances cognitive function in community-dwelling older adults with MCI. The exploratory objective is to characterize the underlying brain-gut axis mechanisms, as assessed by resting-state functional MRI and 16S rRNA gene sequencing of the gut microbiota.

## Methods and analysis

2

### Study design

2.1

This single-blind, randomized controlled trial (ChiCTR2400093397, www.chictr.org.cn) employs a two-arm parallel design, consisting of an intervention group receiving a combination of VRCT, TCT, and PE, and a waitlist control group who will receive no training during the research period. As compensation, the waitlist group will be offered the same training after the follow-up assessment. All participants will undergo comprehensive assessments at four time points: baseline (week 0), mid-intervention (week 6), post-intervention (week 12), and a 12-week follow-up (week 24). The trial is designed in accordance with the CONSORT (Consolidated Standards of Reporting Trials) guidelines and will be conducted and reported accordingly.

### Participants

2.2

The inclusion criteria are as follows: individuals aged between 60 and 80 years who met the International Working Group criteria for MCI (Winblad et al., 2004), Mini-Mental State Examination (MMSE) score of ≥24 (Zhang et al., 2018), Montreal Cognitive Assessment (MoCA) score of ≤26 (Zhang et al., 2018), Patient Health Questionnaire-9 (PHQ-9) score of <5 (Kroenke et al., 2001), and not taking any cognitive-enhancing medications. Exclusion criteria include individuals with major physical illnesses or other psychiatric disorders, those who have difficulty cooperating, or those unwilling to participate in the study. The full list of inclusion and exclusion criteria is presented in Table 1.

**TABLE 1 T1:** Inclusion and exclusion criteria.

Inclusion criteria	Exclusion criteria
1. Right-handed	1. Individuals with major physical or mental illnesses
2. Aged between 60 and 80 years	2. Individuals who are illiterate or unable to comprehend the study content
3. Meets the International Working Group criteria for MCI	3. Individuals with acute exacerbations of cardiovascular, respiratory, or other chronic conditions
4. MMSE ≥ 24	4. History of substance abuse or dependence
5. MOCA score ≤ 26	5. Use of antibiotics or probiotics within 1 month prior to or during the trial
6. PHQ9 < 5	6. Discomfort with VR equipment
7. Not currently taking any cognitive-enhancing medications	7. Severe visual or hearing impairments
–	8. Contraindications to MRI
–	9. Refusal to participate or failure to provide informed consent

MCI, mild cognitive impairment; MMSE, Mini-Mental State Examination; MoCA, Montreal Cognitive Assessment; PHQ9, Patient Health Questionnaire 9; VR, virtual reality; MRI, Magnetic Resonance Imaging.

This study will be conducted in full compliance with the ethical principles of the World Medical Association’s Declaration of Helsinki (2024 revision) for medical research involving human subjects. Ethical approval was obtained from the Ethics Committee of Zigong Mental Health Center (Approval No. 20241102). All participants will be fully informed about the study protocol and will be required to provide written informed consent prior to enrollment.

### Randomization and blinding

2.3

Participants will be randomly assigned in a 1:1 ratio to either the intervention group or the waitlist group using a computer-generated randomization sequence. To ensure baseline balance, randomization will be stratified by MCI subtype (amnestic vs. non-amnestic), baseline MoCA score (19–22 vs. 23–26), and age (60–65, 66–70, or 71–80 years). This approach ensures allocation concealment and minimizes selection bias. Due to the practical challenges of blinding participants, the study was conducted as a single-blind randomized controlled trial. Group allocation was concealed from partial research personnel—including outcome raters and data analysts—with the exception of the therapists administering the interventions, in order to reduce observer bias. All raters are explicitly prohibited from inquiring about participants’ group assignments, and all participants are instructed not to voluntarily disclose their treatment experiences or subjective impressions to raters.

### Interventions

2.4

#### Physical exercise (PE)

2.4.1

The World Health Organization recommends that older adults engage in moderate- to vigorous-intensity physical activity on a weekly basis, as such activities can improve functional capacity and reduce the risk of falls (Bull et al., 2020). In the present study, the intervention group will be instructed to engage in public square dancing, which is popular among middle-aged and older adults in China—three times per week, with each session lasting 30 min, over a 12-week period (totaling 36 sessions). To ensure consistency, all sessions will utilize a fixed set of low-to-moderate intensity, widely-practiced dance routines. These group-based exercise will be led by a trained instructor following a standardized video-audio recording that dictates the movements, tempo, and duration. All participants will be required to wear a wrist-strap heart rate monitor during exercise, with intensity maintained at a moderate level—defined as 50%–70% of the age-predicted maximum heart rate, calculated using the formula: 220 minus age (Hidalgo and Sotos, 2021).

#### Traditional cognitive training (TCT)

2.4.2

Current clinical approaches to TCT for MCI employ heterogeneous protocols, with significant variations in training modalities (Hill et al., 2017) (computerized vs. paper-and-pencil vs. VR), cognitive domains targeted (Sherman et al., 2020) (single-domain vs. multi-domain approaches), intervention parameters (Ren et al., 2024) (session duration, frequency, and total training dose) and theoretical frameworks (Park and Bischof, 2013) (strategy-based vs. process-specific vs. neuroplasticity-focused). Based on our preliminary survey and the level of acceptance among older adults in the community, the TCT program was designed around classical cognitive domains commonly used in cognitive neuroscience, incorporating Card-based Visual Recognition, Spot the Difference, Jigsaw Puzzles, and Sudoku (Table 2). The training targets four key cognitive domains: memory, attention, executive function, and visuospatial ability. After each physical exercise session, the intervention group will complete TCT (15 min per session, three times per week for 12 weeks), with one task randomly selected for each session.

**TABLE 2 T2:** Traditional cognitive training (TCT) and virtual reality cognitive training (VRCT) programs.

Groups	Domains	Programs	Instructions
TCT			
	Memory	Card-based visual recognition task	The therapist prepares picture cards featuring items such as fruits, animals, and vehicles. The participant is first shown each picture one by one. After viewing, the pictures are covered, and the participant is asked to recall and verbally name the items that were shown.
	Attention	Spot the difference task	Place two similar pictures on the table. The participant is asked to pick up the images, identify the differences between them, and mark the areas where the differences are found.
	Visuospatial ability Executive function	Jigsaw puzzles	The participant is presented with puzzle pieces of a chosen image (e.g., nature scenes, animals, or familiar objects). They are asked to observe the shapes, colors, and edges, and gradually fit the pieces together. Puzzle difficulty can be adjusted by changing the number of pieces, complexity of the image, or removing edge pieces.
	Visuospatial ability Executive function	Sudoku	Sudoku chessboard consists of a 9 × 9 grid divided into nine 3 × 3 subgrids. The objective is to fill the grid so that each row, each column, and each 3 × 3 box contains the digits from 1 to 9 without repetition.
VRCT			
	Memory Visuospatial ability Executive function	Memory cards	Various colored pattern cards will appear on the screen, and participants must memorize their shapes and positions within a set time. Once the countdown ends, the cards will flip over, and participants are required to select the correct color or pattern based on the task instructions.
	Attention Visuospatial ability Executive function	Letter-number sequencing	Scattered sequences of numbers or letters will appear in a 3D virtual space. Participants must observe and analyze them carefully, then arrange them according to specific rules.
	Memory Attention Executive function	Butterfly memory	Participants observe butterflies flying across the screen and must remember their quantity, color, and flight order, then select the correct answer according to the task instructions.
	Memory Visuospatial ability Executive function	Supermarket shopping	This training simulates a real-life shopping scenario. Participants read the task instructions, memorize the types and quantities of items to be purchased, and then select the required items from memory.
	Mind-body relaxation	Mindfulness meditation	The system offers 16 VR scenarios designed for mindfulness-based relaxation. Guided by the system’s instructions, participants are led to focus on the present moment through breathing or visualization, promoting a state of physical and mental relaxation.

TCT, traditional cognitive training; VRCT, virtual reality cognitive training.

#### Virtual reality cognitive training (VRCT)

2.4.3

To enhance participant engagement and compliance, we added the VRCT program. VRCT is delivered using the SY-VRD VR system (Shuyun, Chengdu, China). Drawing on preliminary research and participant feedback, we selected four game-based cognitive tasks—Memory Cards, Letter-Number Sequencing, Butterfly Memory, and Supermarket Shopping—designed to target attention, memory, visuospatial skills, and executive function, with each task engaging multiple cognitive domains (Kim et al., 2023; Ren et al., 2024; Table 2). The SY-VRD system incorporates an adaptive algorithm that automatically adjusts task difficulty based on individual performance. Detailed operational procedures and difficulty parameters for each task are provided in the Supplementary materials. Additionally, to optimize intervention adherence and mitigate potential VR-related fatigue, each VRCT session concluded with a 5-min guided mind-body relaxation protocol. A professional therapist is available to guide participants in using the equipment and to offer support as needed; however, all tasks are completed independently by the participants. The intervention group will complete a 15-min VRCT session following each TCT session, with one VRCT task randomly selected for each session.

### Outcome measurements

2.5

The primary outcome is the change from baseline in a memory-weighted cognitive composite score, specifically designed to detect subtle changes over the trial period. This composite integrates tests that assess the cognitive domains most relevant to MCI, including: (1) Verbal learning and memory: total of five learning trials from the Chinese Auditory Verbal Learning Test (AVLT); (2) Delayed recall: 20-min delayed recall trial from the Chinese AVLT; (3) Executive function: Trail Making Test (TMT; Parts A and B); (4) Attention and working memory: Digit Span Test (DST; forward and backward).

To construct the composite score, raw scores from each test will be converted to Z-scores using the mean and standard deviation of the pooled sample at each test time point. For the Trail Making Test, where lower scores indicate better performance, Z-scores will be multiplied by −1 to ensure consistent directionality across all tests (higher Z-scores always indicate better performance). Based on the theoretical importance of memory function in MCI, the AVLT learning and delayed recall scores will receive a weight of 2, while the TMT and DST scores will receive a weight of 1. The final composite score will be calculated as the weighted average of these Z-scores (Andrade, 2021).

Secondary cognitive outcomes include changes from baseline in global cognitive function, assessed using the Montreal Cognitive Assessment (MoCA) and the Mini-Mental State Examination (MMSE). The MoCA provides a comprehensive assessment of multiple cognitive domains with high sensitivity for MCI (Nasreddine et al., 2005), while the MMSE is included to facilitate comparison with prior studies. Subjective cognitive decline will be assessed using the Alzheimer’s Disease 8-item scale (AD8), an informant-based measure that captures perceived changes in memory, orientation, and executive function.

Exploratory outcomes include the following: (1) Changes in gut microbiota alpha/beta diversity and composition assessed by 16S rRNA gene sequencing, (2) Changes in resting-state brain activity and functional connectivity assessed by fMRI. (3) changes in serum metabolites, evaluated via metabolomic analysis; (4) changes in sleep quality, measured by the Insomnia Severity Index (ISI); (5) changes in mood, assessed using the Patient Health Questionnaire-9 (PHQ-9) and the Generalized Anxiety Disorder-7 (GAD-7) scales; (6) changes in daily living abilities, measured by the Instrumental Activities of Daily Living (IADL) and Activities of Daily Living (ADL) scales; (7) changes in gastrointestinal symptoms, assessed using the Gastrointestinal Symptom Rating Scale (GSRS); (8) changes in quality of life, measured by the WHO Quality of Life-OLD (WHOQOL-OLD) scale.

Safety evaluation will include the incidence and severity of all adverse events (AEs), with particular attention to VR-related discomfort (e.g., dizziness, nausea, eyestrain, headache). AEs will be systematically recorded after each training session, and vital signs (blood pressure, heart rate) will be monitored immediately post-session. All AEs will be graded as mild, moderate, or severe based on participant self-report.

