#### Statistical considerations

2.8.2

The analysis will adhere to the eHealth Consolidated Standards of Reporting Trials (CONSORT) criteria (Eysenbach, 2011), follow the intention-to-treat principle and per protocol set. The per-protocol set included participants who attended at least 70% of the assigned intervention sessions and completed all protocol-specified assessments (Zhang et al., 2018). Statistical analyses will be conducted using IBM SPSS Statistics (Version 24.0; IBM Corp., Armonk, NY, United States). Continuous variables are presented as mean and standard deviation; categorical variables as frequency and percentages.

For baseline characteristics, continuous variables are compared between groups using *t*-test, while categorical variables are analyzed using chi-square test. Primary outcomes will be analyzed using two-way repeated-measures ANOVA, evaluating the main effects of group, time, and their interaction. *Post-hoc* pairwise comparisons were conducted with Bonferroni correction for multiple comparisons. Missing follow-up data will be imputed using the last observation carried forward (LOCF) method. Sensitivity analyses (completers-only and per-protocol) will assess potential bias due to dropouts and imputation methods. We will also compare baseline characteristics between participants who dropped out and those who completed the study. All tests are two-sided, with statistical significance defined as *p* < 0.05.

Multimodal neurobiological correlates of treatment response will be assessed by integrating structural/functional MRI, gut microbiome, and plasma metabolome with behavioral outcomes. For analyses involving gut microbiota, key dietary patterns extracted from the 3-day food diaries will be included as covariates to enhance the validity of the findings. Hypothesis-driven analyses will include: (i) partial least squares (PLS) regression to identify multivariate brain-behavior associations, (ii) mixed-effects modeling for longitudinal effects, and (iii) mediation analysis to test whether brain-gut axis changes drive clinical improvement. Significance thresholds will be adjusted via Holm-Bonferroni correction.

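### Re-standardising the primary composite at every visit fixes its pooled mean at zero, so the time effect and within-arm change cannot show absolute improvement, decline or practice; the group-by-time test stays valid but its unit shifts between visits

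*Protocol article*

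**What the plan says.** Protocol article, 2.5 Outcome measurements: "The primary outcome is the change from baseline in a memory-weighted cognitive composite score, specifically designed to detect subtle changes over the trial period". The next paragraph gives the scoring rule: raw scores are "converted to Z-scores using the mean and standard deviation of the pooled sample at each test time point". TMT scores are then sign-reversed, and "the AVLT learning and delayed recall scores will receive a weight of 2, while the TMT and DST scores will receive a weight of 1". Averaging the Z-scores with these weights gives the composite.

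Section 2.8.2 (Statistical considerations) analyses the primary outcome by "two-way repeated-measures ANOVA, evaluating the main effects of group, time, and their interaction", followed by Bonferroni-corrected pairwise comparisons. The component tests are given at weeks 0, 6, 12 and 24 (Table 3). Nowhere does the article fix the reference mean and SD at baseline or at an external norm.

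**The concern.** A Z-score computed against the mean of the same visit discards whatever the whole sample did between visits. If everyone improves through practice, the composite does not move. If the intervention arm improves and the waitlist arm is stable, half of the gain is displayed as a waitlist loss. That conflicts with an outcome defined as change from baseline. It also conflicts with the reason given in the Discussion for replacing the registered MoCA primary outcome, namely better sensitivity to small cognitive changes over 24 weeks. The tests are repeated four times, so practice gains are plausible and one would want to see them.

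The scale is affected as well. The SD at each later visit includes the separation between the arms and any change in spread, so one composite unit at week 12 is not the same quantity as one unit at week 0 or week 24.

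**Working it through.** **Inputs from the protocol article.** Two arms, 1:1, 66 enrolled; four visits; weights AVLT learning 2, AVLT delayed recall 2, TMT 1, DST 1; repeated-measures ANOVA with group, time and interaction.

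**Assumptions, not in the documents.** One Z-score each for TMT and DST; between-visit correlation 0.6; between-test correlation 0.4; no missing data; 2,000 simulated trials per scenario.

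**Planned sample size (2.8.1).** For the within-between interaction, lambda = f²·N·m/(1 − rho). With f = 0.25, N = 46 and, as assumptions, m = 2 measurements and rho = 0.5: lambda = 0.0625 × 46 × 2 / 0.5 = 11.5 on 1 and 44 df, power 0.912. N = 46 is reproduced, and 46/0.70 = 65.7, so 66. The scoring rule does not enter this calculation.

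**Step 1: pooled mean.** At each visit every component Z has pooled mean 0, so the weighted average has pooled mean 0. With arm sizes n0 and n1 and mean changes D0 and D1 (same people at both visits):

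n0·D0 + n1·D1 = 0.

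If n0 = n1, then D0 = −D1 and the time effect is zero. In the simulations the largest absolute D0 + D1 was about 6e-16, the largest time F about 1e-29, and the time effect was rejected in 0% of runs in every scenario. If n0 ≠ n1, or a subset of the standardised set is analysed, the time effect is near zero rather than exactly zero.

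**Step 2: what the reader would see (week 12 minus week 0, waitlist/intervention, SD units).**

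| True change | Scored as planned | Scored against pooled week 0 |
|---|---|---|
| 0 / +0.5 | −0.24 / +0.24 | 0.00 / +0.51 |
| +0.3 / +0.8 | −0.24 / +0.24 | +0.31 / +0.81 |
| −0.5 / 0 | −0.24 / +0.24 | −0.50 / 0.00 |
| +0.5 / +0.5 | 0.00 / 0.00 | +0.51 / +0.51 |

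The first three rows are different clinical courses with one displayed result. In the last row the time effect is significant in 0% of runs as planned and in 100% with baseline scoring.

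**Step 3: the between-arm contrast.** Subtracting the same pooled mean from both arms cancels in their difference. Only the divisor matters. With equal arms, baseline SD 1, within-arm SD s at the later visit and true difference d, the pooled SD is √(s² + d²/4), so the displayed difference is d/√(s² + d²/4).

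- Stable spread (s = 1): d = 0.5 gives 0.485 (loss 3%); d = 0.8 gives 0.743 (7%); d = 1.0 gives 0.894 (11%). Simulated: 0.48 for 0.5 and 0.74 for 0.8.
- Wider spread, assumed: d = 0.5 with s = 1.2 gives 0.5/√(1.44 + 0.0625) = 0.41; with s = 1.3, 0.5/√(1.69 + 0.0625) = 0.38.
- Narrower spread, assumed: d = 0.5 with s = 0.8 gives 0.5/√(0.64 + 0.0625) = 0.60, an inflation.

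**Step 4: the interaction test.** Type I error was 0.049 with no change in either arm and 0.051 with a common practice gain, the same under both scorings. Power for the 0/+0.5 case was 0.735 as planned against 0.759 with baseline scoring. With SD growing to 1.2 times baseline it was 0.59 against 0.66.

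**The case against.** The strongest defence is that the causal question in a randomised trial is the difference between arms. The article's hypothesis is framed relative to the waitlist arm, and the group-by-time interaction is among the planned tests. That contrast survives: its type I error is right and, with stable spread, little is lost. MoCA and MMSE, as secondary outcomes, are not described as re-standardised and can still show absolute change. All of this stands and limits the point.

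A reader might infer more than the documents support:

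- *That the whole primary analysis is an artefact, or that the trial cannot show benefit.* It can show benefit relative to the waitlist arm. Only the time effect and within-arm change are uninterpretable.
- *That the score reduces to ranks.* Z-scoring is linear. Within a visit it keeps relative distances; what is lost is the common origin and unit across visits.
- *That a false waitlist decline is certain.* Section 2.8.2 does not say whether the pairwise comparisons are within arms or between arms at each visit, and the apparent decline arises only when the intervention arm gains more.
- *That the contrast is badly diluted.* The larger losses need an SD ratio such as 1.2 or 1.3, for which the article gives no basis. A narrowing spread would act in the opposite direction.

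The defence does not remove the point, because 2.8.2 lists time, group and interaction side by side without singling out the interaction, and 2.5 defines the outcome itself as change from baseline.

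**Conclusion.** The point holds in limited form. The standardisation rule is explicit and is incompatible with reading the composite as change from baseline. The zero pooled mean follows from algebra and rests on none of the simulation assumptions; exact cancellation of the time effect also needs equal arms and an analysed set equal to the standardised set. Where those conditions fail, as they may in the completers-only and per-protocol analyses, the time effect is still uninterpretable. The ±0.24 figures rest on the assumptions listed with the calculation.

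The primary randomised inference is not invalidated. What it loses is a constant unit, at a cost of a few per cent for moderate effects under stable spread and an unknown amount, in either direction, if spread changes. The correction belongs before unblinding, since a later change to the scoring of the primary outcome would look data-driven.

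**What to change.** In 2.5, replace the standardisation rule with: raw scores at all visits are converted to Z-scores using the week-0 mean and SD of all randomised participants, both arms pooled; the TMT sign reversal and the 2:1 weights are then applied, and these scores are used in every analysis of the composite.

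In 2.8.2, name the group-by-time contrast as the primary test.

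The cost is one sentence in each section and one line of code. No new data are needed, and the figures of 46 and 66 are unaffected. A fixed linear scale also means that carrying forward a raw score or its Z-score gives the same value, so the order of LOCF and standardisation no longer matters.
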